## **Feasibility indicators**

Feasibility indicators include patient recruitment rate, randomization rate, treatment compliance, and subject retention rate. Compliance refers to the proportion of acupuncture courses obtained from the expected course of treatment.

## **Sample size calculation**

Based on previous studies, the average postoperative pain score during coughing for the EA and SA groups is estimated to be  $3.0 \pm 1.7$  and  $4.4 \pm 1.7$ . To achieve a statistical power of 80% with a two-sided significance level of 5%, 24 patients per group are required. Sixty patients (30 per group) are required, accounting for a dropout rate of 20%. This pilot trial is intended to establish initial data for the primary outcome measure, and the results will be used to calculate the sample size for the next larger randomized controlled trial.

## **Statistical analysis**

Statistical analysis will be processed using SPSS Statistics 27. Measurement data will be described as mean  $\pm$  standard deviations ( $M \pm SD$ ), median, or interquartile range. Categorical data will be presented by frequency, percentage, or constituent ratio. Independent t-test or

Wilcoxon rank-sum test will be used to compare the measurement data between groups. The chi-squared test or Wilcoxon rank-sum test will be used to compare the categorical data between groups. The significant level is  $P < 0.05$ , which is considered to be statistically significant.

All randomly assigned patients will be included in the intention-to-treat (ITT) analysis. The per-protocol (PP) analysis, which includes participants completing 80% of the treatment without major protocol deviations or omissions will be used for the primary outcome as sensitivity analysis.

Normally distributed continuous variables will be analyzed using independent t-test. Skewed continuous variables will be analyzed using Wilcoxon rank-sum test. Categorical data will be analyzed using the chi-squared test or Wilcoxon rank-sum test. We will perform a predefined subgroup analysis on primary endpoints according to the chest tube duration, the number of incisions, etc.

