## **Objectives**

This trial aims to assess the feasibility and efficacy of EA with standard care versus SA with standard care for acute postoperative pain after VATS.

Hypothesis testing:

H0: Efficacy of EA = Efficacy of SA

H1: Efficacy of EA  $\neq$  Efficacy of SA

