## **Randomization**

Stratified block randomization will be applied with stratification according to the two research centers and variable block lengths. Sixty eligible patients will be randomly assigned to the EA or SA group in a 1:1 ratio. A statistician not involved in the implementation or statistical analysis of the trial will generate the random sequences using the STATA statistical software (version 12.0; StataCorp LP). The random number is kept by the independent administrator, who does not participate in the trial intervention, evaluation, and statistics. The CRC will contact an independent administrator by phone to obtain randomization information.

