## **Secondary outcomes**

- (1) The average pain score during rest, coughing, and mobilization (moving from the lying to the sitting position) will be measured by NRS (assessment time: 24h, 48h, and 72h after VATS).
- (2) Pain scores during rest and the incidence of CPSP (defined as NRS  $\geq 1$ ) at month 3 after surgery.
- (3) Five-level EuroQol five-dimensional questionnaire (EQ-5D-5L) (assessment time: before surgery and at 24h, 72h, and month 3 after surgery).
- (4) The severity of postoperative cough measured by cough symptom score (assessment time: month 1 and month 3 after surgery).
- (5) The dosage of postoperative analgesic drugs and rescue medication. (assessment time: the whole study period).
- (6) The postoperative pulmonary complications (atelectasis, pulmonary infection, pleural effusion, pneumothorax, etc.) and adverse events of acupuncture and drugs (assessment time: the whole study period).
- (7) First expectorated sputum (assessment time: the whole study period).
- (8) Chest tube duration (assessment time: the whole study period).
- (9) Length of postoperative hospital stay (assessment time: the whole study period).
- (10) Blinding assessment (assessment time: after the second treatment).

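### One unqualified P < 0.05 rule covers about 22 secondary comparisons and an open-ended subgroup analysis; it should be confined to the single primary test

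*Protocol*

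**What the plan says.** The Primary outcome section of the protocol names one endpoint, the average cough NRS within 72 h. The Sample size calculation section powers that endpoint alone: "To achieve a statistical power of 80% with a two-sided significance level of 5%, 24 patients per group are required".

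The Secondary outcomes section lists ten items. The first covers three conditions, each at 24, 48 and 72 h: "The average pain score during rest, coughing, and mobilization (moving from the lying to the sitting position) will be measured by NRS". Cough pain is therefore the primary outcome as a 72 h average and a secondary outcome at each of three times.

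The Statistical analysis section names t, Wilcoxon and chi-squared tests for comparing the groups, and then gives one threshold: "The significant level is $P < 0.05$ , which is considered to be statistically significant". The sentence singles out no outcome. The same section ends with "We will perform a predefined subgroup analysis on primary endpoints according to the chest tube duration, the number of incisions, etc". It mentions no interaction test.

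The Objectives section says "This trial aims to assess the feasibility and efficacy of EA with standard care versus SA with standard care", and its null hypothesis is equal efficacy of the two arms, tied to no endpoint.

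**The concern.** As written, any secondary time point or subgroup level that reaches P < 0.05 may be called statistically significant, in the same words as the primary result. Because the null hypothesis in Objectives is not tied to an endpoint, the protocol does not say that only the primary test decides it.

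Two features add to this. The primary signal can be tested again at 24, 48 and 72 h at the full 5%. And a subgroup list that ends openly is not predefined, so a factor could be added after the data are seen without departing from the text.

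One of the two named subgroup factors has a further problem. Chest tube duration is secondary outcome (8). It is observed after randomisation and the treatment may affect it, so a comparison within its levels no longer sets randomised groups side by side.

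At stake is how secondary and subgroup results are read. The primary test is not at stake.

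**Working it through.** **1. The plan's own figure.** The protocol states no error rate across several tests, so the only figure to reproduce is the sample size. Its inputs, from Sample size calculation, are means of 3.0 and 4.4 (difference 1.4), SD 1.7, two-sided 5%, power 80% and 20% dropout. Allocation is 1:1 (Randomization).

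n per group = 2 × (1.960 + 0.842)² × 1.7² / 1.4² = 23.1, rounded up to 24. Then 24 / (1 − 0.20) = 30 per group, 60 in total. Both stated figures are reproduced. The calculation uses one test at 5%, so nothing below changes it.

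**2. Count of secondary efficacy comparisons (Secondary outcomes).**

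| Item | Comparisons |
|---|---|
| (1) NRS, 3 conditions × 3 times | 9 |
| (2) Rest pain and CPSP at month 3 | 2 |
| (3) EQ-5D-5L, 3 postoperative times | 3 |
| (4) Cough symptom score, 2 times | 2 |
| (5) Analgesic dose, rescue dose | 2 |
| (6) Pulmonary complications, as one composite | 1 |
| (7) First sputum | 1 |
| (8) Chest tube duration | 1 |
| (9) Postoperative stay | 1 |
| **Total** | **22** |

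Adverse events, the blinding assessment and the preoperative EQ-5D-5L are left out. Without pulmonary complications the total is 21.

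**3. Chance of at least one P < 0.05 among the 22 under no effect.** If the tests are independent, it is 1 − 0.95²² = 0.676. The expected number of false positives is 22 × 0.05 = 1.1, whatever the correlation.

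The outcomes come from the same patients and will be correlated, but the protocol gives no correlations, so these are assumptions. The table shows 400,000 simulated sets of two-sided z-tests with a common correlation r:

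| r | 22 secondaries | 9 NRS tests only |
|---|---|---|
| 0 | 68% | 37% |
| 0.3 | 57% | 33% |
| 0.5 | 44% | 27% |
| 0.7 | 30% | 20% |
| 0.8 | 23% | not needed |

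A structure that is closer to this mix of outcomes sets correlation at 0.5 to 0.8 within a domain and 0 to 0.3 between domains. It gives 46% to 60% for the 22.

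**4. Subgroups.** The protocol gives neither levels nor cut-points. Suppose each factor has two levels and the named two-group test is run inside each level. Two factors then give 4 tests and three give 6. Independence would give 1 − 0.95⁴ = 18.5% and 1 − 0.95⁶ = 26.5%. The factors divide the same 60 patients, so the tests overlap. Simulating null trials of 60 patients with random two-level factors gives about 16% for two factors and 22% for three.

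**The case against.** The strongest objection is that multiplicity handling, exploratory labels, subgroup levels and interaction tests commonly belong in a statistical analysis plan, and none is shown here. That stands: the absence of an adjustment method from the protocol is no finding. What remains is text that the protocol does contain, namely a threshold with no restriction and a list called predefined but left open. An analysis plan that labelled the secondaries exploratory would have to qualify that threshold.

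A reader might infer that the protocol has no hierarchy at all. It does have one: a single primary outcome stands apart from the secondaries, it alone is powered, and the per-protocol and subgroup analyses are confined to it. What is not stated is any limit on what a significant secondary or subgroup result may be taken to show.

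A reader might also infer that the trial's 5% error rate is breached several times over. The stated 5% belongs to the primary test, and that test keeps it. The protocol sets no error rate for the whole set of tests, so none is broken.

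Finally, the protocol calls the trial a pilot. That softens the point but does not remove it, because the same document powers the trial at 80% and states an efficacy hypothesis. A reader might go on to suppose that chance findings will choose the endpoint or population of the next trial. The protocol says only that the results will be used to calculate its sample size, so that harm is not documented.

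**Conclusion.** The point holds in a limited form. The significance rule is broader than the one test for which the trial was sized, and the subgroup sentence contradicts itself. The primary comparison and the sample size of 60 are sound on this point.

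Under no effect, the chance of at least one nominally significant secondary is about 23% to 68%, and the chance within subgroups is about 16% to 22%. The first range rests on the count of 22 and on assumed correlations from 0.8 to 0. The second rests on two or three two-level factors with separate tests in each level, which the protocol does not specify.

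It is tempting to say that a chance positive is likely. That holds only at low to modest correlation; at a common correlation of 0.5 or more the chance is below one half. Even the lowest figure is well above 5%, which is reason enough to correct the wording.

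**What to change.** In the Statistical analysis section of the protocol:

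- Limit the P < 0.05 decision to one test, the intention-to-treat comparison of mean cough NRS over 72 h.
- State that all secondary outcomes, including cough NRS at 24, 48 and 72 h, and all subgroup analyses are exploratory and will be reported as estimates with 95% confidence intervals.
- Replace the open subgroup list with a closed one, restricted to factors fixed before the first treatment session. Chest tube duration does not qualify. The number of incisions does, since it is settled at surgery and the first session follows the return to the ward.
- Assess each factor by a treatment-by-subgroup interaction, with its estimate and interval, and not by separate tests within levels.

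The change costs a few sentences and needs no further patients or data. The downside is that secondary and subgroup results can no longer be called statistically significant.

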## **Outcomes**

### **Primary outcome**

The average postoperative pain score during coughing is recorded using NRS within 72 h after surgery.

NRS scale is an effective tool to evaluate pain, with high reliability and validity, easy to record, and widely used. The scale requires patients to rate themselves according to the degree on a 10-point scale, which is divided into 1-10 grades. According to the corresponding figures, the pain can be divided into different degrees, and the middle from 0-10 represents the pain of different degrees that gradually increases. 0 is no pain, 1-3 is mild pain, 4-6 is moderate pain, and 7-10 is severe pain.

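### Randomisation is stratified by centre, but the primary comparison is an unadjusted test chosen by the observed distribution; it should be fixed in advance as a model with group and centre

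*Protocol*

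**What the plan says.** Protocol, Randomization: "Stratified block randomization will be applied with stratification according to the two research centers and variable block lengths". Centre is the only stratification factor. Allocation is 1:1 over sixty patients.

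Protocol, Primary outcome: "The average postoperative pain score during coughing is recorded using NRS within 72 h after surgery".

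Protocol, Statistical analysis: "Normally distributed continuous variables will be analyzed using independent t-test. Skewed continuous variables will be analyzed using Wilcoxon rank-sum test". The same pair of tests is also named earlier in that section for measurement data. There is no centre term, no separate rule for the primary outcome, and no criterion for calling a variable normal or skewed.

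Protocol, Sample size calculation: the means are taken as 3.0 (EA) and 4.4 (SA) with SD 1.7 in each arm. "To achieve a statistical power of 80% with a two-sided significance level of 5%, 24 patients per group are required". The section calls the trial a pilot and adds that "the results will be used to calculate the sample size for the next larger randomized controlled trial".

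**The concern.** Two features of the stated method do not fit the design.

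First, stratified allocation balances the arms within each hospital, so a difference between hospitals largely cancels out of the treatment contrast. The two-sample standard error still contains that difference as if it were noise. It is then too large, the test runs below its nominal 5% level, and precision that the stratification made available goes unused.

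Second, a t-test compares means and a rank-sum test compares rank distributions. The Protocol sizes the trial on a mean difference but lets the observed distribution decide which quantity the primary test addresses. The primary treatment effect is therefore not fixed before the data are seen, and without a criterion the choice is open to discretion.

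The Protocol itself names these tests, so this is a stated method and not a detail left for a statistical analysis plan.

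**Working it through.** **Inputs from the Protocol.** Difference 4.4 − 3.0 = 1.4; SD 1.7; two-sided alpha 5%; power 80%; dropout 20%; two centres; 1:1 allocation.

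**Inputs assumed.** The difference δ between hospitals in mean cough NRS is not given; the range 0 to 2.0 points is used. The centre split is not given; 50/50 is used, which makes the centre effect largest. The Protocol does not say whether 1.7 is a within-centre or a total SD, so both readings are shown.

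**The plan's own figure.** n = 2 × (1.960 + 0.842)² × 1.7² / 1.4² = 23.1, so 24 per group; 24 / 0.8 = 30 per group, 60 in total. Both reproduce. With the noncentral t distribution, power is 79.8% at 24 per group and 88.0% at 30.

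**Mechanism.** With equal centres, total variance = within-centre variance + δ²/4. The contrast varies with the within-centre SD, but the t-test divides by the total SD. The effective critical value is therefore the nominal one times (total SD / within-centre SD).

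Example, δ = 1.0, 24 per group (46 degrees of freedom, critical value 2.013):
- 1.7 as within-centre SD: total SD = √(2.89 + 0.25) = 1.772; 2.013 × 1.772 / 1.7 = 2.098; two-sided tail 4.1%.
- 1.7 as total SD: within-centre SD = √(2.89 − 0.25) = 1.625; 2.013 × 1.7 / 1.625 = 2.106; two-sided tail 4.1%.

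**Simulation.** 200,000 normal-data trials per cell, 24 per group, 12 per arm per centre; unadjusted t-test against a linear model with group and centre. The adjusted model's type I error was 4.9 to 5.1% throughout.

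| δ (NRS) | Type I unadjusted: 1.7 within / 1.7 total | Power unadjusted vs adjusted, 1.7 within | Power unadjusted vs adjusted, 1.7 total | Power forgone (points) |
|---|---|---|---|---|
| 0 | 5.0% / 5.0% | 80% vs 80% | 80% vs 80% | 0 |
| 0.5 | 4.8% / 4.8% | 79% vs 80% | 80% vs 81% | 0.6 |
| 1.0 | 4.1% / 4.0% | 77% vs 80% | 81% vs 83% | 2.5 to 2.6 |
| 1.5 | 3.3% / 2.9% | 74% vs 80% | 82% vs 87% | 5.5 to 5.8 |
| 2.0 | 2.2% / 1.6% | 69% vs 80% | 84% vs 93% | 9.0 to 10.6 |

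Smaller runs of 20,000 trials agree within simulation error of a few tenths of a point for type I error and up to about a point for power.

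**With 30 per group analysed.** Unadjusted power for the five values of δ is 88, 88, 86, 84 and 80% if 1.7 is the within-centre SD, and 88, 88, 89, 90 and 92% if it is the total SD.

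**With a 70/30 centre split** (24 per group, 1.7 as total SD). At δ = 2.0 the unadjusted type I error is 1.9% and the power forgone is 90.6 − 82.8 = 7.8 points, somewhat less than with equal centres.

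**Choosing the test from the data.** Simulated on normal, rounded NRS, averaged NRS, gamma and lognormal data with 24 or 30 per group. Choosing by a Shapiro-Wilk test in each arm gave type I error of 4.3 to 5.4%, close to that of the fixed tests. Taking the smaller of the two p-values, the worst case of a free choice, gave 5.1 to 6.7%.

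**The case against.** The other side has substance. No difference between the hospitals is documented, and at 0.5 points or less the effect is negligible. A difference of 2.0 points would exceed the assumed treatment effect of 1.4. The equal split is the least favourable one, the plan recruits 30 per group, and the intention-to-treat analysis is to include everyone randomised. All of this stands and limits the size of the point. It does not remove the mismatch, because adding centre costs nothing measurable when the hospitals do not differ.

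Four stronger readings might be inferred, and the Protocol does not support them:
- *The trial risks false positives from ignoring centre.* The error is in the other direction: below 5%, and only if the centres differ.
- *The planned power is lost.* That needs both 1.7 as a within-centre SD and attrition to about 24 per group. Otherwise power stays at about 80% or more, and what is lost is the gain that adjustment would bring.
- *Choosing between t-test and rank-sum test distorts the error rate.* Under a fixed normality rule it barely moves. The modest rise needs a free choice, which the missing criterion permits but the Protocol does not propose.
- *The next trial would have no mean difference to plan from.* The Statistical analysis section lists mean and SD among its summaries, so these can be reported whichever test is used. The wording offers them as one of several options, so it does not guarantee them.

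**Conclusion.** The point holds in a limited form. The stated primary comparison leaves out the one factor used to stratify allocation, and it leaves open until the data are seen whether means or ranks are compared, although the sample size rests on a mean difference. The cost from omitting centre depends on an unknown hospital difference: nothing at zero, negligible at 0.5 points, about 2.5 points of power at 1.0, and about 9 to 11 points at 2.0, with a conservative test throughout. These figures assume normal data, 24 per group and equal centres. The case for fixing the primary effect measure holds even if the hospitals do not differ. In a 60-patient pilot the importance is modest, but the change is worth making because it is almost free.

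**What to change.** In the Protocol's Statistical analysis section, name one primary analysis in advance: a linear model of mean cough NRS over 72 h on treatment group and centre, reporting the adjusted mean difference with its 95% CI whatever the observed distribution. Keep a rank-based test as a sensitivity analysis only. Extending centre adjustment to the secondary outcomes is optional.

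The cost is one degree of freedom and a few lines of wording. At 24 per group with no centre difference, power is the same to within 0.1 point with or without the centre term. The model can be fitted with the general linear model procedure in SPSS, the package the Protocol already names. No change to recruitment, data collection or sample size is needed.

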## **Background**

Video-assisted thoracoscopic surgery (VATS) has become the primary surgical approach in thoracic surgery. Compared with thoracotomy, VATS is notable for less trauma, lower postoperative pain levels, better quality of life, shorter length of hospitalization, and lower complication rates. Despite numerous analgesic strategies in clinical practice, including thoracic epidural analgesia, paravertebral block, and patient-controlled analgesia, acute postoperative pain still exists after VATS.

Acute postoperative pain is closely related to operation time, chest tube duration, and postoperative activities. After surgery, doctors will encourage patients to cough to promote the expulsion of respiratory secretions, but patients may be afraid to cough forcefully due to postoperative acute pain. About 59% of patients experienced moderate to severe acute pain during the first three days after VATS. In contrast, postoperative pain when coughing is often more severe than when resting. Approximately 51.7% of patients experienced moderate to severe pain when coughing within the first 24 hours after surgery. On postoperative day 7, around 20% of patients were still encountering moderate and severe pain while coughing.

Notably, inadequate management of acute postoperative pain frequently results in chronic post-surgical pain (CPSP). About 43.99% of patients reported CPSP after VATS, and the incidence of moderate or severe chronic

pain is 14.71% among them. CPSP will reduce the quality of life of patients and affect their physical and mental health. The efficacy of drug treatment is limited for CPSP at present. Acute postoperative pain control and prevention of CPSP still lack effective interventions.

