### 2. Interventions

Patients will receive four sessions of EA or SA within 72 h after surgery (treatment timepoint 1: upon patients return to the ward, treatment timepoint 2: 6 h after surgery, treatment timepoint 3: at 2 pm on postoperative day 1, and treatment timepoint 4: at 2 pm on postoperative day 2). Each treatment will continue for 30 minutes.

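### The primary endpoint is to be split by chest tube duration, a secondary outcome known only after treatment has begun, so the within-subgroup effects are open to bias

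*Protocol*

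**What the plan says.** The protocol's Statistical analysis section ends with this commitment: "We will perform a predefined subgroup analysis on primary endpoints according to the chest tube duration, the number of incisions, etc".

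Four other places bear on it:

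- **Secondary outcomes, item (8):** "Chest tube duration (assessment time: the whole study period"). The same variable is therefore an endpoint on which the two arms are compared.
- **Background:** "Acute postoperative pain is closely related to operation time, chest tube duration, and postoperative activities".
- **Interventions:** the first of four sessions is given at "treatment timepoint 1: upon patients return to the ward", with later sessions up to postoperative day 2.
- **Primary outcome:** "The average postoperative pain score during coughing is recorded using NRS within 72 h after surgery".

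Randomisation is stratified by centre only ("Stratified block randomization will be applied with stratification according to the two research centers and variable block lengths"). Nowhere does the protocol treat chest tube duration as a baseline variable or allow for its being observed after treatment starts.

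**The concern.** A subgroup analysis asks whether the treatment effect differs between kinds of patient. Within each subgroup the two arms must still be comparable. Randomisation secures this when the subgroup is defined by something treatment cannot have influenced, and chest tube duration is not such a variable. The protocol tests it as an outcome, and it is fixed only at tube removal, once sessions have begun.

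Suppose EA shortens tube time. Some EA patients who would have had long drainage under sham then move into the short-duration group. The EA patients left in the long-duration group are a more adverse selection than the SA patients there. The short-duration EA group has likewise taken in less favourable patients. If those patients also tend to have more pain, the arm difference within each subgroup mixes the treatment effect with this selection.

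What is at stake is how a planned secondary look at the primary endpoint will be read. Being specified in advance guards against choosing subgroups after seeing the data. It does not restore comparability within a subgroup formed on an outcome. The trial is a pilot meant to inform a larger one, so a subgroup result could influence later planning.

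**Working it through.** **1. The plan's own figure.** The Sample size calculation section gives means of 3.0 and 4.4 with SD 1.7, so the difference is 1.4. The normal-approximation formula gives

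n per group = 2 × (1.96 + 0.8416)² × (1.7/1.4)² = 23.1, rounded up to 24.

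With 20% dropout, 24/0.8 = 30 per group, 60 in total. The protocol's 24, 30 and 60 are reproduced. (An exact t-test calculation gives 24.1 per group and 79.8% power at 24, which is immaterial here.) None of this depends on the subgroup plan.

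**2. Order of events.** The first session is on return to the ward. Tube duration is known at removal, which is later. The protocol does not state the moment of randomisation, but tube duration follows it on any reading.

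**3. Size of the possible bias.** The inputs are:

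- From the protocol: SD 1.7 and true difference 1.4 (taken as the same in every patient), 1:1 allocation.
- Assumed, not in the documents: within-arm correlation ρ between pain and tube duration of 0 to 0.5; EA shortening tube duration by d = 0 to 0.5 SD; joint normality; split at the pooled median.

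With the arms centred at −d/2 and +d/2 around the pooled median, the selection difference between arms is the same in both strata:

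k(d) = φ(d/2) × [1/Φ(−d/2) − 1/Φ(d/2)]

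The bias in the treatment difference is ρ × 1.7 × k(d), towards zero when EA works. For d = 0.5:

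k = 0.3867 × (1/0.4013 − 1/0.5987) = 0.318.

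At ρ = 0.5 the bias is 0.5 × 1.7 × 0.318 = 0.27; at ρ = 0.3 it is 0.3 × 1.7 × 0.318 = 0.16.

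A simulation of 2 million patients per scenario agrees. It gives these EA minus SA differences, to within 0.01 in both strata (truth −1.40):

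| Shortening by EA | ρ = 0 | ρ = 0.3 | ρ = 0.5 |
|---|---|---|---|
| 0 SD | −1.40 | −1.40 | −1.40 |
| 0.25 SD | −1.40 | −1.32 | −1.26 |
| 0.5 SD | −1.40 | −1.24 | −1.13 |

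The largest entry is a bias of 1.40 − 1.13 = 0.27, and 0.27/1.4 = 19%. At a 0.5 SD shift, 60% of EA patients but 40% of SA patients fall in the short-duration group. A larger assumed shift would extend the range: 0.8 SD with ρ = 0.5 gives −0.97.

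**4. Bias against noise.** With 60 patients and two equal strata there are about 15 per arm per stratum. The standard error of a within-stratum difference is 1.7 × √(2/15) = 0.62. The 95% interval is about ±2.048 × 0.62 = ±1.27 (t on 28 degrees of freedom). A bias of 0.27 is 0.27/0.62 = 0.44 of one standard error.

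**The case against.** The strongest reply is that bias is not shown. It needs an EA effect on tube duration and a within-arm association of tube duration with pain; if either is absent the bias is zero, as the first row and first column of the table show. Listing tube duration as an outcome means it will be compared, not that EA is expected to change it, and the Objectives mention only feasibility and efficacy for acute pain. The Background asserts a relation with pain but gives no size. This stands: the effects are open to bias, not biased with certainty.

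The second reply is that the analysis is ancillary, in a pilot, with so few patients per stratum that random error exceeds the plausible bias. This also stands, and it limits the severity. It does not rescue the choice of variable, because imprecision does not make the comparison a randomised one.

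The third reply is that a statistical analysis plan, not shown here, may settle the detail. That is fair for cut-points, interaction tests and the full list of factors, so the open-ended close of the subgroup sentence is not counted as an error. It does not answer the main point: a cut-point or an interaction test would still condition on a post-randomisation outcome.

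A reader might also infer that the split would manufacture a false finding that EA works only in patients with short drainage. The calculation does not support that: the attenuation is practically the same in both strata, so no spurious contrast between them appears under this model. Nor can it be said how many patients would be classified using information from after the 72-hour window, because the protocol gives no expected tube duration.

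**Conclusion.** The point holds in this form. The protocol fixes, as a subgroup factor for the primary endpoint, a variable that it also lists as an outcome, that is realised after treatment begins, and that it describes as closely related to pain. The within-subgroup differences do not compare groups formed by randomisation and are open to bias.

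The range of 0 to about 0.27 NRS points (0 to 19% of 1.4) rests on the protocol's SD and difference and on assumed values for the correlation, the shift, the normal model and the median split. It illustrates the mechanism and is not an estimate for this trial.

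A reader might infer that the trial's main conclusion is compromised. It is not: the primary intention-to-treat comparison does not use the split, and 24 per group and 60 in total stand. This is a should-fix.

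**What to change.** Remove chest tube duration from the subgroup sentence in the Statistical analysis section and analyse it only as secondary outcome (8). Restrict subgroup factors to variables fixed before the first session. The number of incisions, already named, qualifies because it is settled at surgery.

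The change costs one sentence, needs no new data and leaves the sample size as it is. The downside is that the split by drain duration is no longer reported as a treatment-effect subgroup. If the investigators wish to keep it, it should be presented only as a descriptive, non-causal analysis, with a note that the groups are defined by a post-randomisation outcome.
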